#### Intervention: short-term intensive psychodynamic group therapy

The form of short-term intensive psychodynamic group therapy to be used in this trial has been manualized by the research team for the study. The manual describes the aims of the treatment, specifies the therapist’s tasks and purposes, presents the therapist’s interventions, and outlines the kinds of problems and conflicts that can be found in this patient group. The manual also provides examples of session situations that are typically encountered in a day hospital setting. The manual is based on the team’s experience and on some elements of available manuals. It is rooted in the group analysis tradition [59], and is based on the group analytic psychotherapy manual as developed by [name] [47]. The manual was adapted for the day treatment setting and also draws on Polish psychoanalytical group experiences as practiced in public service [58–60, 81]. This approach was initiated in the 1960s and has evolved since then.

The intervention shares the five basic assumptions of the psychodynamic approach formulated by Rutan [68]. The first is psychological determinism: the assumption that our actions are more or less determined, like our way of perceiving and recognizing. The second is unconscious processes, namely that predetermined influences may to a great degree be unconscious. The third is dynamic and goal-directed behavior: according to the dual-instinct theory, a person’s behavior serves to protect the individual from perceived danger or pain, whereas according to the object-relation theory, the behavior of a person is directed to reach a relationship and attachment. Psychology of the self claims that the goal is to formulate and strengthen the integrated self. The fourth is epigenetic development: the unconscious life of the individual originates in relation to interpersonal experiences remaining from before. People are unconsciously forced to repeat those experiences which are connected with a majority of conflicts and painful experience. Flaws in early development can be repaired if they are relived and effectively re-experienced correctively in the here and now of the transference. Finally, the assumption that different functions of mind are at work at any time, and distinct functions (id, ego, superego) may be in conflict with one another. In this approach, all anxiety disorder symptoms are understood as an expression of unacceptable unconscious fantasies and conflicts. This approach also shares the assumption that the current conflict, which is activated under the influence of current life events, is a reflection of a conflict of the past [48]. Due to the short form of the therapy, its goals are formulated realistically by taking into account the symptoms of personality disorders.

The main therapeutic factors are: 1) mirroring, namely that patients can recognize their own aspects in the fantasies, behaviors, and problems of other group members; 2) sharing, namely that patients share information, which helps them to understand themselves, their interactions with others, and their own problems; and 3) condenser phenomena, namely that unconscious material is easily expressed through the common influence of group members on one another. Shared associations help to understand the symbolic significance of experiences. Additionally, universal group factors are taken into account [87]. The therapists use techniques of clarification, confrontation, and interpretation. As in other psychodynamic short-term therapies, this approach is more structured. To intensify the therapeutic processes, three additional techniques are used: 1) memoir, namely that each patient describes his or her own life story, which consists of important emotional experiences, and reads it during one therapeutic session; 2) elements of role playing and/or psychodrama, namely that the patient presents his or her way of talking to important persons; 3) a summary, namely that patients receive written structured feedback from other patients in the final stage of therapy.

Application of these techniques results from the need for patients to concentrate on the therapeutic goals and for greater structuralization in patients with personality disorders. It is characteristic of this type of therapy to observe and discuss the manner of how a patient interacts with other patients in a group and with the therapist (transference), and afterwards to relate this to the patient’s functioning in past relations and in other relations beyond the therapy. A significant factor is exploring and modifying immature defense mechanisms, with a major focus on the mechanisms of projection and acting-out, and on increasing the employment of mature defense mechanisms. The group process is of great importance; it is assumed to have both a conscious and unconscious aspect. The course of therapy consists of phases that are supposed to stimulate various conflicts in different patients. The therapists are more active here than in the classical form of group analysis: they employ interventions more often, such as explaining and naming reality, and are less focused on patients’ fantasies. In classic group analysis, the group therapist does not function as a group leader but as a group conductor, frustrating regressive needs and thus replacing the leader’s authority by that of the group: all members interpret, analyze, and support one another, including the conductor [43].

#### Intervention: short-term intensive transdiagnostic cognitive-behavioral group therapy

The short-term intensive transdiagnostic cognitive-behavioral group therapy (GCBT) was designed to conduct treatment in naturalistic settings of diagnostically mixed anxiety disorder patients with comorbid personality disorders [36]. It is based on the transdiagnostic approach to emotional disorders, and particularly anxiety disorders, which has been in development for over the past 10 years [4, 5, 55]. Additionally, it includes interventions for personality disorders based on schema therapy and modes of personality disorders. This approach assumes high overlap between anxiety disorders and is focused on their common aspects. Preliminary data indicate that GCBT is equally effective in the treatment of individuals with different anxiety disorders [56].

The short-term intensive GCBT that has been developed by our group shares the classical assumptions of CBT [6], namely that the emergence and persistence of psychopathological symptoms results from maladaptive thinking styles and cognitive bias (the cognitive model), and maladaptive behavioral strategies (the behavioral model). Anxiety disorders in particular are described as resulting from distorted beliefs focused on threat (physical or psychological) and an elevated sense of personal vulnerability [9]. Therefore, short-term intensive GCBT, just like standard CBT, is focused on helping patients identify and modify distorted cognitions, and on using techniques based on learning principles, mainly exposure, to help them eliminate anxiety.

Short-term intensive GCBT, similarly to most CBT therapies, is task-oriented and designed for finding and solving problems. Among the therapeutic techniques there are: monitoring and identification of negative automatic thoughts and related emotional experiences, physical sensations and behaviors (in the form of diaries), various techniques for restructuring and challenging dysfunctional thinking, creating a hierarchy of anxiety-provoking situations, performing exposure (imaginal and *in vivo*), behavioral experiments, relaxation techniques, developing goal-setting and problem-solving skills, and social skills training [41]. What differentiates GCBT from CBT is that the strength of group cohesion is employed, that is, a sense of belonging and confidence in the group’s members and believing that its goals are important [77, 87]. GCBT creates a good environment for such phenomena as modeling, social learning, and exposure. Participating in the group gives the patient the opportunity to employ characteristic group therapeutic factors, such as hope, universality, information sharing, altruism, corrective recapitulation of primary family experience, social skills development, and imitation [87].

The GCBT therapy process is divided into modules that reflect the phases and stages of the therapeutic process ([name] and [name], unpublished work). A weekly schedule includes cognitive therapy and behavioral therapy (exposure, *in vivo*) sessions as well as social skills training, including mainly assertiveness. As a result of such a schedule, each week consists of four elements: a homework discussion (weekend task), the presentation of new material during psychoeducation and therapy sessions, training new skills (examples from the lives of patients, role play, and exposure), and planning the next homework assignment. As a result, patients learn new skills, practice them in a safe environment, and then gradually introduce them into their lives outside the group.

### Assessments

Patients are subjected to four assessments: 1) at the screening; 2) at baseline after randomization; 3) at the end of the 12-week treatment; and 4) six months after the end of therapy in order to evaluate the longer-term effects of the treatments. Patients in the wait-list group will have one additional assessment at the end of the 12-week waiting period.

Information from the screening will be used to perform stratified randomization and to validate the inclusion and exclusion criteria. Patients will be assessed by independent and trained clinicians who will remain blind to the treatment conditions, and who will not be involved in direct clinical care of any of the patients. Primary outcome measures and secondary outcome measures can be distinguished in this study. The primary outcome measures include self-report symptoms of anxiety, observer-rated symptoms of anxiety, global improvement, and dichotomized diagnosis of anxiety disorder (improved or unimproved). The secondary outcome measures include personality, depression, self-esteem, defense mechanisms, beliefs about self and others, interpersonal problems, object relations, parental bonding, meta-cognition, and quality of life. The following sociodemographic data will be collected: sex, age, marital status, education, past treatments, symptom history, and medication. We will also examine patients’ expectancy toward change and treatment. Some of the variables, such as the presence or absence of a personality disorder, will be treated in exploratory analyses as predictors and moderators of treatment response. The time points of assessment and measures are presented in Table 3.

**Table 3 Tab3:** Instruments at different assessment points

Instrument	Screening	Baseline	End of Treatment	6-Month Follow-up
STAI		X	X	X
HAM-A		X	X	X
CGI-S		X	X	X
CGI-I		X	X	X
M.I.N.I.	X		X	X
SCID-II	X			
BDI-II	X		X	X
OQ-45		X	X	X
SES		X	X	X
DSQ-40		X	X	X
PBQ		X	X	X
IIP		X	X	X
DWM-S		X	X	X
ECR		X	X	X
BORRTI		X	X	X
MCQ		X	X	X
SWLS		X	X	X
CEQ		X		

STAI: State-trait anxiety inventory; HAMA-A: Hamilton anxiety rating scale; CGI-S: Clinical global impression - severity scale; CGI-I: Clinical global impression - improvement scale; M.I.N.I.: Mini-international neuropsychiatric interview 5; SCID II: Structured clinical interview for DSM-IV personality disorders questionnaire; BDI-II: Becks depression inventory II; OQ-45: Outcome questionnaire; SES: Self-esteem scale; DSQ-40: Defense style questionnaire; PBQ: Personality beliefs questionnaire; IIP: Inventory of interpersonal problems; DWM-S: Dysfunctional working models scale; ECR: Experiences in close relationships; BORRTI: Bell object relations and reality testing inventory; MCQ: Meta-cognitions questionnaire; SWLS: Satisfaction with life scale. CEQ: Credibility/Expectancy questionnaire

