The inclusion and exclusion criteria are listed in Table 1. The number of excluded patients and the reasons for exclusion will be recorded. The diagnostic criteria are based on the DSM-V system. Initial assessment will be conducted with independent researchers who will not be involved in the further interventions. It will include a pharmacological consultation by a psychiatrist, personality diagnosis with SCID-II [24, 25], and diagnosis of clinical disorders with the Mini International Neuropsychiatric Interview 5^1^ (MINI) [71, 51]. Diagnosis and evaluation for treatment will be carried out during ambulatory sessions. The focus of the treatment is on psychotherapy, but medication will be continued or initiated if necessary during the screening procedure at least four weeks before the beginning of group psychotherapy (stable medical treatments with selective serotonin re-uptake inhibitors or serotonin-norepinephrine reuptake inhibitors, without dose changes during psychotherapy unless necessary). Baseline measurements and final adjustments of pharmacological treatment will be conducted one day before the beginning of therapy. Randomization will take place during the last diagnostic session. Participants will be randomized using random number tables. A recruitment flow chart is presented in Fig. 1. Patients are planned to be enrolled in the study for over a period of three years. Before participating in the study, each patient will be provided with written information about the study and will be invited to give written consent for inclusion. Participants who do not meet the inclusion criteria will be offered suitable alternative treatment options.

**Table 1 Tab1:** Inclusion and exclusion criteria

Inclusion criteria	Current diagnosis of Axis I anxiety disorder (based on the MINI)
	Diagnosis of comorbid personality disorder (based on the SCID II) or depressive disorder (based on the MINI)
	Aged 18 to 65-years-old
	Sufficient knowledge of the Polish language
	Written informed consent from the patient
Exclusion criteria	Organic brain disorder
	Acute substance-related disorders
	Schizophrenia or bipolar affective disorder
	Severe depression (defined as over 26 points on the Beck Questionnaire)
	Cluster A personality disorders
	Current suicidal ideation and a high risk of suicide
	Restricted intellectual capacity
	Serious unstable medical problems or complications
	Concurrent psychotherapeutic treatment

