### Statistical analysis

All data analyses will be performed using SPSS Statistics software v21.0 (IBM Corporation, Armonk, NY, USA). All randomized patients will be analyzed, including those who stop receiving treatment, on an intention-to-treat (ITT) as well as treatment-completer basis. The multiple imputation method will be used for missing data when appropriate. Analyses of variance with repeated measures (three measurement points: pre, post, and follow-up) will be applied for continuous data (primary outcomes: STAI, HAM-A, CGI-S, and CGI-I; secondary outcomes: BDI-II, OQ-45, SES, DSQ-40, PBQ, IIP, DWM-S, ECR, BORRTI; MCQ, and SWLS). Primary planned comparison is the interaction between the time (pre-to-post and post-to-follow-up change on anxiety) and group variables (CBT versus wait list; PDT versus wait list). Chi-squared tests will be applied for dichotomous data (MINI). Additionally, random effects models for repeated measures will be used. Multiple regression analyses will be applied to test moderators of change that is to show whether each of the interventions is more effective for some groups of patients (interventions, diagnoses, combination of diagnoses and baseline measurements as predictors). Multiple regression analyses will be also applied to search for mediators of change that are theory-specific (for example, changes in beliefs for CBT and changes in defense mechanisms for psychodynamic therapy). We will take into account to what extent the patients were exposed to the intervention by analyzing the dose-effect relationship.

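### STAI, HAM-A and CGI-S are first measured after randomisation, and the primary test on change passes any effect of allocation on that baseline straight into the treatment effect

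*Protocol article*

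**What the plan says.** The section on recruitment, criteria and randomisation fixes the allocation: "Randomization will take place during the last diagnostic session". The same paragraph places the baseline: "Baseline measurements and final adjustments of pharmacological treatment will be conducted one day before the beginning of therapy". The Assessments section confirms the order by listing the second and third assessments as "2) at baseline after randomization; 3) at the end of the 12-week treatment".

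The screening visit comes before allocation, but its stated purpose is narrower: "Information from the screening will be used to perform stratified randomization and to validate the inclusion and exclusion criteria". In Table 3, STAI, HAM-A and CGI-S are marked at baseline, end of treatment and follow-up, and not at screening. The MINI and the BDI-II are marked at screening.

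The Statistical analysis section states: "Primary planned comparison is the interaction between the time (pre-to-post and post-to-follow-up change on anxiety) and group variables", with each therapy set against the wait list. No baseline covariate is named. A second model is mentioned only as a supplement: "Additionally, random effects models for repeated measures will be used".

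**The concern.** A baseline is a safe reference point only if allocation cannot have affected it. Here a therapy-arm patient fills in the STAI, which includes situational anxiety, knowing that an intensive programme starts the next day. A wait-list patient answers in the knowledge that treatment is 12 weeks away, or on a date that the article does not state separately. If that knowledge moves the score, the arms differ at baseline for a reason other than chance, and randomisation no longer protects the comparison of change.

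With two time points, the time-by-group interaction is the difference between arms in mean change. A baseline difference caused by allocation therefore becomes part of the estimated effect. Separately, where baseline is sound, a change score is less precise than the 12-week score adjusted for baseline.

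**Working it through.** **Inputs from the article** (Sample size calculation): effect against wait list d = 0.58, alpha 0.05, power 0.80, 159 patients for the 3 × 2 interaction at f = 0.25, and 199 to be recruited.

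**Assumed, because the article gives neither:** the correlation ρ between baseline and 12-week score (0.3, 0.5, 0.7), and the shift δ in baseline caused by knowing the allocation (0.1, 0.2, 0.3 SD). The shift is taken not to persist to 12 weeks. Scores have SD 1 at both times.

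**Step 1: the plan's own figure.** A noncentral F calculation with noncentrality N·f², f = 0.25 and three groups gives N = 159 (power 0.805), as stated. 159 × 1.25 = 198.75, which gives 199. 159 / 3 = 53 per arm, used below.

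**Step 2: bias.** Let θ be the true effect and δ the baseline difference, therapy minus wait list, caused by allocation.

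- Difference in change: θ + δ.
- 12-week score adjusted for the post-allocation baseline: θ + ρδ.
- 12-week score adjusted for a pre-allocation baseline: θ.

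Against the planned effect: 0.1 / 0.58 = 17%, 0.2 / 0.58 = 34%, 0.3 / 0.58 = 52%.

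**Step 3: false positives.** The standard error of the difference in change is √(2 × 2(1 − ρ) / n). At ρ = 0.5 and n = 53 it is √(2 / 53) = 0.194. With no true effect, shifts of 0.1, 0.2 and 0.3 SD lie 0.51, 1.03 and 1.54 standard errors from zero, and the two-sided 5% test rejects in 8.1%, 17.7% and 33.9% of trials.

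A simulation of 20,000 trials at δ = 0.2 and ρ = 0.5 agrees:

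| Analysis | Bias (SD) | Rejection rate |
|---|---|---|
| Change score | 0.20 | 17.4% |
| Adjusted for post-allocation baseline | 0.10 | 8.9% |
| Adjusted for pre-allocation baseline | 0.00 | 4.8% |

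**Step 4: precision when there is no shift.** The variance factor is 2(1 − ρ) for change and 1 − ρ² for the adjusted score. The ratio is (1 + ρ) / 2. For d = 0.58:

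| ρ | Variance ratio | Power at 53 per arm, change → adjusted | n per arm for 80%, change → adjusted |
|---|---|---|---|
| 0.3 | 0.65 | 71.3% → 87.9% | 66 → 43 |
| 0.5 | 0.75 | 84.7% → 93.2% | 47 → 35 |
| 0.7 | 0.85 | 97.1% → 98.7% | 28 → 24 |

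**Step 5: if the earlier baseline is less predictive.** Let r be its correlation with the 12-week score. Adjustment on it beats change from the later baseline only if 1 − r² < 2(1 − ρ), that is r² > 2ρ − 1. At ρ = 0.5 any r above 0 suffices. At ρ = 0.6, r must exceed 0.45; at 0.7, 0.63; at 0.8, 0.77.

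**The case against.** The strongest reply is that the bias is conjecture, and that holds for its size and sign. A reader might infer that anticipatory anxiety inflates the apparent benefit of both therapies. The article does not support that: relief at being offered therapy, or disappointment at having to wait, would push the other way. HAM-A and CGI-S are rated by clinicians blind to condition, and the STAI also has a trait scale, so the mechanism fits self-reported state anxiety best. What the article does show is that the order of visits leaves the door open.

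A reader might also infer that the wait list has no comparable baseline because its therapy starts only after the wait. That goes too far. The Assessments section gives the wait list an additional assessment at the end of the wait, and the sample size section says that all three groups can be compared at two measurements. A pre-wait baseline is implied; only its date is not stated separately.

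Third, with a sound baseline the interaction test is valid in a randomised trial, and covariate adjustment is then a gain in efficiency. This stands. The gain is also small at ρ = 0.7. At about 66 per arm (199 / 3, ignoring loss of information from dropout) the change test alone has power of about 80%, 91% and 99% at ρ = 0.3, 0.5 and 0.7. The precision argument supports the fix but would not carry the point by itself.

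Two neighbouring matters should not be added. That the analysis section does not mention stratification factors is a detail a condensed article can leave to the full plan. The adjustment of medication on the baseline day is a separate question from when the outcome scales are taken.

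**Conclusion.** The point holds as a design weakness. STAI, HAM-A and CGI-S have no pre-allocation value, and the primary comparison is built on change from a post-allocation one. No analysis plan written later can supply a measurement that was never taken.

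How much this would matter is not known. The percentages and error rates above follow from an assumed shift and correlation, and they are illustrations of sensitivity. The order of visits and the one-for-one transmission into change are certain; the existence of a shift is not. It would also be wrong to infer that a pre-allocation baseline removes bias altogether. It removes the part that enters through baseline. Patients still know their treatment when they complete the STAI at 12 weeks, and the article's Discussion already concedes that a wait list controls poorly for expectancy.

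The change should be made, because it is cheap and the weakness is avoidable.

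**What to change.** Collect STAI, HAM-A and CGI-S at the last diagnostic session, before the allocation is drawn and at the same point in all three arms. Make the primary comparison the 12-week score with that baseline as a covariate. Keep the score from the day before therapy as descriptive only. Both parts are needed: adjusting for the post-allocation baseline alone leaves a bias of ρδ, for example 0.5 × 0.2 = 0.10 SD.

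The cost is one reordered set of measurements and a change of analysis wording. Table 3 already has the BDI-II at screening, and the Trial status section expected recruitment to begin only in September 2015, after publication. There are two downsides. The gap between baseline and the start of therapy becomes longer, which may lower the correlation with outcome (step 5). The wait-list assessment must also be aligned so that the interval from baseline to the 12-week score is the same in every arm; the date of the wait-list baseline should be stated for this purpose.
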